### Intervention

#### Intervention group

The SDTICA program was developed by our research team in consultation with art therapists, neurology experts, clinical nurse specialists, and social workers. The SDTICA program will consist of a 27-session syllabus of 45–60 min per session. A group approach of 8–10 people per group will be used [57]. If experienced facilitators are available, we will consider increasing the number of participants. The program will focus not only on cognitive enhancement, but also on psychological health and social interaction as well as engagement in meaningful leisure activities. The SDTICA program will be conducted in a nursing home activity room, and will be led by two experienced and qualified instructors who have been trained in AT and have certified proficiency and experience in teaching art methods to older adults. Furthermore, the nursing home will provide two more social workers (to assist in guiding activities) and a care worker (to provide medical security) to assist with the program. Program implementation will take into account participant engagement and study feasibility. According to MRC guidance for the development and evaluation of complex interventions, the program will be pretested in terms of feasibility via a pilot study [58]. The protocol of the SDTICA program is detailed in the Additional file.

There is evidence [59] that the activity theme integrating traditional cultural elements with Chinese characteristics and nostalgic elements is more suitable for the psychological characteristics of older adults in China and effectively stimulates the creative enthusiasm and interest of participants. Therefore, the program will combine the historical background experienced by older adults; integrate the elements of traditional Chinese culture and nostalgia; and cover the four theme types of “traditional festivals, historical nostalgia, exploration of imagination, and general themes”. Each session, which is structured and pre-planned during the study, will be divided into four phases: Phase 1 involves 5–10 min for introduction and warm-up activities, which are made up of thematic-related art materials exploring body warming or music games. Phase 2 involves 5 min for topic discussion. Instructions will be provided with written steps/slides showing the task sequence. During a conversation, participants will be questioned on a shared theme. Importantly, thematic exploration and discussions will build on the participants’ existing experience or foundation. Phase 3 involves 30 min for art production. In the form of peer support, participants will be asked to draw or create anything they consider relevant to the theme. Phase 4 involves 10 min for sharing, summary, and feedback. Participants will be encouraged to show and briefly introduce their own works within the scope of the group, and voluntarily share their feelings and experiences. The instructor will summarise the activity according to the participants’ feedback on the activity. In addition, regular art work exhibitions will be held to to recognise the efforts of the participants (e.g., art works will be pasted on art walls or placed on display cases). Additionally, possible adverse events including related to adherence to the study and participants’ attrition will be tracked and closely monitored by the instructor and other staff involved in the intervention.

Based on SDT, this program will be divided into three structural stages: (1) prophase, which focuses on relatedness and involves setting up a support group and using pair work between peers to help participants integrate into the group and be familiar with a wide variety of art materials; (2) metaphase, which focuses on competence and involves providing clear instructions/tips and guidance (e.g., through video, audio, and pictures related to the theme), inspiring participants to think and discuss, and guiding participants to explore various types of activities in order to gain relevant abilities; and (3) anaphase, which focuses on autonomy and involves providing creative art types and art materials for participants to choose from in the same event and encouraging them to create freely under specific themes in order to carry over creative abilities beyond the intervention. Before the intervention, we will hold health knowledge lectures and distribute MCI prevention knowledge handbooks to explain why older adults with MCI need to participate in the program. After the intervention, we will conduct the focus group to explore perceived benefits and personal barriers of participants and give them positive feedback regarding the intervention. In addition, we will combine session requirements, autonomy support strategies [60], and the behaviour change techniques by Michie et al. [61] to develop SDT-based behaviour change techniques (focus on relatedness, competence, and autonomy) suitable for this study; this will help promote participants’ autonomy motivation and adherence to intervention. The SDT-based behaviour change techniques are detailed in the Additional file.

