## Methods/Design

### Study design, setting, and ethics

The study is a cluster randomised, controlled, single-blind, parallel-group, multicentre trial conducted on older adults with MCI to assess the effects of the SDTICA program on cognitive function, mental health, and other health-related outcomes (Fig. 1). It will be conducted in nursing homes in Fuzhou City, China.

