### Randomisation, blinding, and allocation concealment

Cluster randomisation will be used to ensure blinding and avoid contamination between groups [40]. Randomisation will occur after participant recruitment, informed consent, and complete baseline assessment. A nursing home is referred to as one cluster in this study. We will randomly select eligible nursing homes from all five-star nursing homes in order to minimize the baseline differences in environment, facilities and equipment, operation management, and service provision. A researcher (not involved in participant recruitment and evaluation) will perform the randomisation of nursing homes via lottery. Allocation will be concealed from the assessors.

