### Data collection

Data collection for the outcome variables pertaining to participants with MCI will be performed in nursing homes by trained researchers. Data will be collected at three time points: baseline, after 14 weeks of intervention, and at 24 weeks of follow-up. To reduce the risk of measurement bias, outcome assessors and statistical analysts will be blinded to the intervention and control allocation and will not be involved in the implementation of the intervention. Data will be encoded independently by two research associates, and inconsistencies will be double checked with the data source to ensure data accuracy.

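### Allocation by nursing home does not ensure assessor blinding: outcomes are collected inside the homes, and exhibitions of residents' art there may reveal the arm, mainly at week 14.

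*Protocol article*

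**What the plan says.** The section on study design, setting, and ethics describes a "cluster randomised, controlled, single-blind, parallel-group, multicentre trial". The section on randomisation, blinding, and allocation concealment makes three relevant statements:

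- "Cluster randomisation will be used to ensure blinding and avoid contamination between groups".
- "A nursing home is referred to as one cluster in this study".
- "Allocation will be concealed from the assessors".

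The Data collection section says that outcome data collection "will be performed in nursing homes by trained researchers". It then gives the safeguard against measurement bias: "outcome assessors and statistical analysts will be blinded to the intervention and control allocation", with neither group taking part in delivery.

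The Intervention group section places the programme in an activity room of the home. To recognise participants' efforts, "regular art work exhibitions will be held"; as an example, "art works will be pasted on art walls or placed on display cases". Control homes receive usual care for 14 weeks.

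**The concern.** Participants know whether they attend art sessions, so the single blind of this trial rests on the assessors and analysts. The protocol credits cluster randomisation with securing that blind. For assessors, the effect runs the other way. In an individually randomised trial, art on a wall would not show which residents had been treated. Here one home has one arm, so a single cue applies to every trial participant in the building.

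The exhibitions are a planned part of the programme in intervention homes only, and the assessors are sent into those homes. The article's own procedures therefore work against its blinding statement. At stake is detection bias in MoCA and MMSE, which stand among the primary outcomes, and in the secondary tests of memory, language, attention and executive function. Any such bias would be aligned with treatment arm. The planned mixed-effects model accounts for clustering, but it cannot separate an arm-aligned scoring difference from a treatment effect, and adding residents would not average it out.

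**Working it through.** The protocol gives no figure on this point, so the check is a side-by-side reading.

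1. **Who is blinded.** Assessors and analysts (Data collection; allocation is also concealed from assessors under randomisation).
2. **Where assessors work.** In the nursing homes (Data collection).
3. **What carries the allocation.** The home (randomisation section). Knowing the arm of one participant means knowing the arm of all participants in that home.
4. **What differs visibly between arms.** Intervention homes run sessions in their activity room and hold regular exhibitions of works, while control homes receive usual care (Intervention group; Waitlist control group). Residents, and the home's social workers and care worker who assist, also know about the sessions and could mention them.
5. **Inference.** Steps 2 to 4 give an assessor a route to the allocation of a whole home. Nothing in cluster randomisation closes that route.

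Exposure by visit:

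| Visit | Exposed? | Reason |
|---|---|---|
| Baseline | No | Randomisation follows the complete baseline assessment |
| Week 14 | Yes, most clearly | Programme just finished in intervention homes; control homes have had usual care only |
| Follow-up | Uncertain | At week 24 the programme ended 24 − 14 = 10 weeks before; control homes may have received it by then |

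Table 1 and Data collection place follow-up at week 24, whereas Data analysis names week 36. The later date would leave the cue no more certain.

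Exposure by outcome:

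- MoCA and MMSE are two of the seven primary instruments, and they are administered by researchers.
- The cognitive domain tests, including verbal fluency and clock drawing, are secondary and are exposed in the same way.
- Self-rated measures, such as the Self-Rating Anxiety Scale, are open to participants' own knowledge of their arm. Hiding the works from assessors would not change that.

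**Scale only, not an estimate.** The sample-size section uses MoCA means of 24.68 and 23.13, a difference of 24.68 − 23.13 = 1.55 points. If assessors in intervention homes scored 0.25 or 0.5 points higher on average, the shift would be 0.25/1.55 = 16% or 0.5/1.55 = 32% of that difference. Both shifts are assumptions. The document supports no particular value, and zero is possible.

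**The case against.** The strongest reply is that the text does not show assessors will see anything. Art walls and display cases are given only as an example. Their place in the home is not stated, nor is whether works remain up between exhibitions or during assessments. They could be confined to the activity room, testing could take place elsewhere, and an assessor might take the works for ordinary decoration. This stands. A reader might infer that one look will reveal the arm of every resident, or that all assessments in intervention homes will be unblinded. The documents support only that this may happen.

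A second reply is that safeguards exist. Allocation is concealed from assessors, they do not deliver the programme, and the person who randomises takes no part in evaluation. Room choice and the handling of displays are details that an article may leave to a fuller document. That is fair, and their absence is not the point. The point is what the article does state: that a design feature ensures blinding when it does not, alongside in-home assessment and scheduled exhibitions.

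Third, the blinding sentence does not say whose blinding is meant and could refer to residents of control homes. But the only parties the protocol names as blinded are assessors and analysts, so readers will take it to cover them.

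Fourth, a reader might take the percentages above as the likely inflation of the effect. They only restate an assumed shift. That unmasked scoring would favour the intervention is a reasonable worry, but it is not documented.

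**Conclusion.** The point holds in a limited form. Home-level allocation does not ensure assessor blinding, and the protocol's own procedures leave a plausible route to unmasking for all participants of a home at once. The exposure is mainly at week 14. It concerns MoCA and MMSE among the primary outcomes and the cognitive tests among the secondary ones. The size and direction of any bias cannot be derived from the document.

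The conclusion assumes that displays, or talk about the sessions, can reach assessors during in-home visits; nothing in the article rules this out. It does not depend on the assumed score shifts. It is not a reason to doubt the design as a whole, but the correction is cheap enough that it should be made before the first week-14 assessment.

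**What to change.** 1. Test in a room with no works on view, and cover or take down displays elsewhere in the home during the week-14 and follow-up assessment windows.
2. Ask residents and staff not to mention activities to assessors.
3. Have assessors record their guess of arm at each post-baseline visit, and report the results by arm.
4. Reword the sentence in the randomisation section so that cluster randomisation is justified by avoiding contamination between groups. Describe assessor blinding separately, through the steps above.

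The cost is minor logistics in each home, one item on the assessment form and one changed sentence. The exhibitions are meant to recognise participants' efforts, so taking works down touches a programme component. Limiting this to the assessment windows keeps the interruption brief.

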**Fig. 1 Fig1:**
[figure not shown]
Flow diagram of the study design

The nursing homes will be randomised on a 1:1 basis to the intervention (SDTICA program) or waitlist control (usual care) group. The waitlist control group will receive the usual care provided by the nursing home, and the intervention group will be exposed to the SDTICA program by professionally trained and qualified intervenors. The SDTICA program design will follow the Medical Research Council (MRC) guidelines on the evaluation and development of complex interventions [40]. A pilot trial will be conducted to assess the acceptability, safety, and feasibility of the SDTICA program. This study will be conducted, analysed, and reported in accordance with the Consolidation Standards of Reporting Trials (CONSORT) statement for cluster RCTs [40]. All procedures will be conducted in accordance with the Declaration of Helsinki. Ethics approval has been granted by the Ethics Committee of Fujian Provincial Hospital (K2022-05-015) and was registered in the Chinese Clinical Trials Registry with registration number ChiCTR2200061681 (trial registration data available at: http://www.chictr.org.cn/edit.aspx?pid=166566&htm=4).

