#### Waitlist control group

Participants in the control group will engage in usual care delivered within the nursing home for 14 weeks after the baseline assessment. If the SDTICA program improves cognitive function and psychological indicators after 14 weeks, it will be applied after obtaining the consent of participants in the waitlist control group as compensation for their participation. Moreover, it can reduce the influence of participant expectation on intervention effect.

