#### Neuropsychological assessments

##### Primary outcome

The primary outcomes, which include global cognitive function and psychological indicator, will be measured using the MoCA, MMSE, Geriatric Depression Scale [62], Zung Self-Rating Anxiety Scale [63], General Needs Satisfied Scale [64], Memorial University of Newfoundland Scale of Happiness [65], and Quality of life-Alzheimer’s disease questionnaire [66].

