##### Secondary outcomes

The secondary outcomes include daily activity function, social function, and specific domains of cognitive function. Specific domains of cognitive function were measured as follows: (1) memory using the Auditory Verbal Learning Test [67], (2) executive function using the Shape Trail Test [68], (3) language using the Category Verbal Fluency Test [69] and Boston Naming Test [70], (4) attention using the Digit Span Test [71], and (5) executive function using the Clock Drawing Test [72]. Daily activity function will be evaluated with ADL. Social function will be assessed using the Lubben Social Network Scale [73] and FAQ. The cited references provide more information on the sensitivity and specificity of the measurement tools.

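### The only stated adverse-event surveillance is by the staff who deliver the program, with no parallel procedure for control homes, so harms and withdrawal reasons would be ascertained unequally

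*Protocol article*

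**What the plan says.** The article's only sentence on adverse events closes the description of the sessions under Intervention group. Its subject is "possible adverse events including related to adherence to the study and participants’ attrition", and it says that these "will be tracked and closely monitored by the instructor and other staff involved in the intervention".

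For the other arm, the Waitlist control group section says: "Participants in the control group will engage in usual care delivered within the nursing home for 14 weeks after the baseline assessment". It names no recording of adverse events or of reasons for leaving, and nobody to do it.

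Outcome data are handled differently. Under Data collection, "Data will be collected at three time points: baseline, after 14 weeks of intervention, and at 24 weeks of follow-up", by trained researchers, and "outcome assessors and statistical analysts will be blinded to the intervention and control allocation". The same sentence keeps these people out of program delivery. Neither that section nor Table 1 lists adverse events or withdrawal reasons for either arm.

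Safety is a stated aim of the pilot only: "A pilot trial will be conducted to assess the acceptability, safety, and feasibility of the SDTICA program". In the main trial, the Primary outcome section begins "The primary outcomes, which include global cognitive function and psychological indicator" and the Secondary outcomes section begins "The secondary outcomes include daily activity function, social function, and specific domains of cognitive function". Data analysis names no safety comparison.

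**The concern.** The article does more than leave harms to another document. It names the observers, and they are the program's own staff. Two problems follow.

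First, opportunity. These staff meet intervention participants repeatedly, and the article gives them no role in control homes during the 14 weeks. Events such as falls, distress or hospital admission can happen to nursing-home residents with or without an art program. A count from one arm, with no count obtained the same way in the other, does not show what the program adds.

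Second, judgement. Whoever delivers a program is not a neutral observer of its harms. The article applies this principle to its efficacy outcomes, where assessors are blinded and separate from delivery in order to limit measurement bias. The adverse-event rule does the reverse.

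The same sentence ties adherence and attrition to adverse events. Reasons for leaving therefore have a stated process in the intervention arm only. What is at stake is any later statement that the program was as safe as usual care, or that people left the two arms for similar reasons. Unequal ascertainment during the trial cannot be repaired at analysis.

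**Working it through.** The article gives no figure for harms, so there is none to reproduce. The check sets its statements on harms, attrition and data collection side by side.

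| Feature | Intervention homes | Control homes | Section |
|---|---|---|---|
| Stated adverse-event observer | Instructor and other program staff | None stated | Intervention group; Waitlist control group |
| Stated contacts at which events are watched for, weeks 0 to 14 | Up to 27 sessions | None stated | Intervention group; Waitlist control group |
| Adverse events or withdrawal reasons in the assessment schedule | Not listed | Not listed | Table 1; Data collection |
| Outcome assessments by blinded researchers | 0, 14 and 24 weeks | 0, 14 and 24 weeks | Data collection; Table 1 |
| Attrition allowance | Part of 15% of the total | Part of 15% of the total | Sample size determination |

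**Size of the asymmetry in observation.** Sessions last 45 to 60 minutes. Full attendance gives 27 × 45 = 1,215 minutes (20.25 hours) to 27 × 60 = 1,620 minutes (27 hours) of observed contact per intervention participant. The stated counterpart in control homes is zero. This measures opportunity to notice events; it does not count events.

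**What that does to a comparison.** Let the true proportion with an event be *p* in both arms, so that the program adds no harm. Let *c₁* and *c₀* be the fractions of events that get recorded in the intervention and control arms.

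- Recorded proportions: *p c₁* and *p c₀*.
- Recorded difference: *p(c₁ − c₀)*.
- Recorded ratio: *c₁/c₀*.

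Whatever *p* is, the recorded ratio equals the ratio of capture, and it is 1 only if capture is equal. The article gives no basis for assuming that. If control events are not recorded at all, *c₀* = 0 and no ratio exists. The direction is not certain either: program staff see more, which raises *c₁*, but they also judge their own program, which could lower it.

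**Withdrawal reasons against withdrawal numbers.** The 14- and 24-week assessments are made by researchers outside program delivery, and the article does not restrict them by arm. A missed assessment therefore shows in either arm. The 15% allowance is applied to the total sample, and Data analysis commits to CONSORT reporting for cluster trials. The number lost is thus known in both arms. Only the reason for leaving has a stated process in one arm and none in the other.

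**Whether control homes could do the recording.** Before a home is accepted, the prefeasibility step under Nursing home recruitment and screening checks that social and care workers are available, and the eligibility criteria require personnel support. Homes are randomised after that. The right type of staff should therefore be present in both arms; what is missing is a stated duty.

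**The case against.** The strongest reply is that this is silence, not error. The sentence describes how sessions run. It does not say that nobody else records events, and a journal article condenses a full protocol that may contain a control-arm form. That stands in part: one cannot conclude that control homes will have no harms record. But the article does state a rule with named observers, and in the 14-week comparison those observers have no stated work in control homes. If a parallel procedure exists, one sentence settles the matter.

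A second reply is that no comparison is spoiled, because none is planned: safety is an aim of the pilot, and the main trial's outcomes are cognitive, psychological, social and functional. That also stands. A reader might infer that a planned safety analysis fails, or that safety can never be compared. The documents support only the conditional statement that a between-arm reading of harms, if made, would rest on unequal ascertainment.

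Three further inferences go too far:

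- **Attrition goes unrecorded in control homes.** It does not, because the scheduled assessments reveal it in both arms.
- **The multiple imputation is undermined.** Under the usual missing-at-random assumption, imputation works from observed data. Reasons for leaving help in judging that assumption but are not a required input.
- **A number of uncompared events can be stated.** Neither an event rate nor the number of homes is given, so any such count would be assumed.

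**Conclusion.** The point holds in limited form. The only stated adverse-event surveillance is by unblinded staff who deliver the program, and no parallel procedure is stated for control homes. As written, any between-arm reading of harms or of withdrawal reasons would be subject to unequal ascertainment.

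The stated opportunity for observation is up to 27 sessions in one arm against none in the other. The resulting bias cannot be quantified from the article, and its direction is not certain. The efficacy analysis and the count of participants lost to follow-up are unaffected.

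The conclusion assumes that the article's rule is the operative one. It would fall away if the full protocol already sets equal recording in both arms. The change is worth making before data collection, since it is cheap then and impossible afterwards, but the trial's main question does not depend on it.

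**What to change.** Record adverse events and reasons for withdrawal on one short form, at the same time points and by the same type of staff in both arms.

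- **Who:** nursing-home care staff, not the blinded outcome assessors, because a reason such as tiring of the sessions would reveal allocation.
- **When:** at the post-intervention and follow-up time points already scheduled, in every home.
- **Reporting:** by arm.
- **Kept separate:** instructors' session notes and adherence, as a record for the intervention arm only.

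The alternative is to state that harms will be described for the intervention arm only and that no comparative safety conclusion will be drawn.

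The cost is a few minutes of form completion per participant. There are two downsides. The form would lean partly on home records or on recall, and recall is a weakness in people with cognitive impairment. Care staff would also know their home's allocation, so the form equalises the procedure between arms without blinding it.
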